# REFOCUS Trial: protocol for a cluster randomised controlled trial of a pro-recovery intervention within community based mental health teams

**DOI:** 10.1186/1471-244X-11-185

**Published:** 2011-11-23

## Abstract

**Background:**

There is a consensus about the importance of 'recovery' in mental health services, but the evidence base is limited.

**Methods/Design:**

A two centre, cluster randomised controlled trial. Participants are community-based mental health teams, and service users aged 18-65 years with a primary clinical diagnosis of psychosis. In relation to the REFOCUS Manual researchintorecovery.com/refocus, which describes a 12-month, pro-recovery intervention based on the REFOCUS Model, the objectives are: (1) To establish the effectiveness of the intervention described in the REFOCUS Manual; (2) To validate the REFOCUS Model; (3) To establish and optimise trial parameters for the REFOCUS Manual; and (4) To understand the relationship between clinical outcomes and recovery outcomes. The hypothesis for the main study is that service users in the intervention arm will experience significantly greater increases in measures of personal recovery (as measured by the QPR) compared to service users receiving care from control teams. The hypothesis for the secondary study is that black service users in the intervention arm will experience significantly greater increases in measures of personal recovery (as measured by the QPR) and client satisfaction (as measured by the CSQ) compared to Black service users receiving care from control teams.

The intervention comprises treatment as usual plus two components: recovery-promoting relationships and working practices. The control condition is treatment as usual. The primary outcme is the Process of Recovery Questionnaire (QPR). Secondary outcomes are satisfaction, Goal setting - Personal Primary Outcome, hope, well-being, empowerment, and quality of life. Primary outcomes for the secondary study will be QPR and satisfaction. Cost data will be estimated, and clinical outcomes will also be reported (symptomatology, need, social disability, functioning).

29 teams (15 intervention and 14 control) will be randomised. Within each team, 15 services users will be randomly chosen, giving a total sample of 435 service users (225 in intervention and 210 in control). Power for the main study: 336 service users will give power to detect a medium effect size of 0.4 (alpha 0.05, power = 0.8) on both QPR sub-scales. Power for the secondary study: 89 participants will give power to detect an effect size of 0.67 on both QPR sub-scales and on CSQ. A range of approaches are used to minimise bias, although service users and clinicians cannot be blinded.

**Discussion:**

This cluster-RCT will evaluate a pro-recovery intervention in community mental health teams.

**Trial registration:**

ISRCTN: ISRCTN02507940

## 1. Background

There is a policy and professional consensus about the importance of 'recovery' in mental health services, defined as "a way of living a satisfying, hopeful, and contributing life" even with any limitations caused by illness [1-4]. This has recently been elaborated: "Recovery is the process of regaining active control over one's life. This may involve discovering (or rediscovering) a positive sense of self, accepting and coping with the reality of any ongoing distress or disability, finding meaning in one's experience, resolving personal, social or relationship issues that may contribute to one's mental health difficulties, taking on satisfying and meaningful social roles and calling on formal and/or informal systems of support as needed" [5].

The REFOCUS Study is a research programme funded through the National Institute for Health Research Programme Grants for Applied Research scheme (RP-PG-0707-10040). The REFOCUS Trial is part of the REFOCUS Study. The REFOCUS Trial is evaluating an intervention (described in the REFOCUS manual [6]) based on the REFOCUS Model, which is derived from wider research [7] and specifically informed by a systematic review and narrative synthesis of personal recovery [8]. The REFOCUS Model is shown in Figure 1.

**Figure 1 F1:**
[figure not shown]
**The REFOCUS Model**.

There is a robust evidence base, including several systematic reviews, for the key elements of the intervention, including the contribution of coaching [9,10], values [11,12], strengths [13,14] and goal-striving [15,16]. This is the first intervention to evaluate their combined use in a complex intervention in adult community mental health services in the NHS in England. The intervention is based on systematic reviews [8] and international best practice [17], and informed by research into staff-service user relationships [18,19] and stigma [20]. Evaluation of the intervention is particularly timely given the current emphasis on recovery and the associated concept of well-being [21] in English mental health services. The results of the trial will be of relevance to (a) developing mental health policy and associated clinical guidelines; (b) clinical practice.

The experiences of recovery of individuals from minority ethnic backgrounds have been insufficiently researched, so a secondary study is being conducted to examine trial outcomes for participants from black backgrounds.

Understanding the relationship between clinical and recovery outcomes is vital if debates about the future direction of mental health services are to be informed by evidence. These debates are happening [22], and the empirical evidence base is very limited [23]. This study will address this knowledge gap.

## 2. Methods/design

### Objectives and hypotheses

#### The REFOCUS Trial has four objectives

**Objective 1: To establish the effectiveness of the intervention described in the REFOCUS manual**, using outcome evaluation to demonstrate that service users receiving care from intervention teams make more progress towards their personal recovery than those receiving care from control teams. The primary outcome measure (QPR) and the secondary outcome measures are listed in Section 13. All outcomes pertain to the individual level and include both staff and service user outcomes.

Main study hypothesis: Service users in the intervention arm will experience significantly greater increases in measures of personal recovery (as measured by the QPR) compared to service users receiving care from control teams.

Secondary study hypothesis: Black service users in the intervention arm will experience significantly greater increases in measures of personal recovery (as measured by the QPR) and client satisfaction (as measured by the CSQ) compared to Black service users receiving care from control teams.

**Objective 2: To validate the REFOCUS Model**, using process evaluation to investigate the extent to which the intended consequences of the intervention are predicted by the REFOCUS Model.

**Objective 3: To establish and optimise trial parameters for the REFOCUS Manual**, including recruitment and retention issues, fidelity, outcome and economic evaluation, implementation strategies, missing data analysis, and sample size calculation

**Objective 4: To understand the relationship between clinical outcomes and recovery outcomes **comprising recovery outcomes of hope, empowerment, well-being, quality of life and personal recovery, and clinical outcomes of symptomatology, needs and social disability.

### Design

This is a two centre cluster-randomised controlled trial, with paired teams randomised to receive the intervention or standard care/treatment as usual arms of the trial. The recovery intervention will be delivered by all members of staff who provide a clinical input to the team.

The intervention will be provided to a complete team, using implementation strategies to support individual practitioners to introduce and maintain these changes. To minimise contamination, the unit of randomisation and analysis is the mental health team. To understand the impact of the intervention a process evaluation will be undertaken.

### Ethics and trial registration

Ethical approval was obtained from East London REC 3 approval 11/LO/0083 on 22.2.11. The trial registration number is ISRCTN02507940 http://www.controlled-trials.com/isrctn.

### Study setting

The intervention will be evaluated in two Mental Health Trusts: South London and Maudsley NHS Foundation Trust (SLaM) and^2^gether Partnership NHS Foundation Trust in Gloucestershire.

SLaM is the largest mental health Trust in the UK, has an annual income of £330 m, spent across over 100 sites spanning urban and suburban settings. It employs 4,500 staff in 296 teams, works with 34,128 service users, and provide adult mental health services across four Boroughs (Croydon, Lambeth, Lewisham, Southwark). These services are provided through Clinical Academic Groups (CAGs). CAGs bring together clinical services, research, education and training for the benefit of patient care. People who use SLaM services are ethnically diverse, with 37% of people using SLaM services recorded on the clinical information system as coming from a 'Black African', 'Black Caribbean' or 'Black other' background.

^2^gether is a rural/semi-rural Trust, employing 806 staff in 23 adult mental health teams, and working with 4,301 service users. People who use^2^gether services are ethnically homogenous, with a very small number of black individuals using services. Therefore the secondary study will be conducted in SLaM only.

### Sample

Team inclusion criteria

• Adult, community-based mental health team (due to the diversity in in-patient provision [24,25])

• Any Complex Care or Promoting Recovery team in the SLaM Psychosis Clinical Academic Group (CAG) or any in^2^gether

• Provide a care co-ordinating function

Service user inclusion criteria

• Aged 18-65 years

• Primary clinical diagnosis of psychosis, e.g. schizophrenia, schizo-affective disorder, bipolar disorder

• No immediate plans for discharge or transfer

• Not currently receiving in-patient care or in prison

• Speaks and understands English

• Not participating in substantial other study

• Has participating paired staff

• In opinion of clinician, is sufficiently well to participate

• In regular contact with at least one worker in the team

Service user exclusion criteria

• Service users who are unable to give consent or are too unwell to be interviewed (in the opinion of clinician)

• No participating paired staff

• Service user whereabouts unknown or service user is uncontactable

Additional service user inclusion criteria for secondary study

• From black African, black Caribbean, black British or black other backgrounds

Staff inclusion criteria

• Provides clinical input into a team included in the trial

• Does not also provide clinical input into a team allocated to the opposite arm of the trial.

• In addition, paired staff completing staff-rated service user measures are in regular clinical contact with service users who are recruited into the trial.

### Sample size

#### Main study

The primary outcome is the Process of Recovery Questionnaire (QPR) [26]. This measure was chosen as the only service user-rated measure of personal recovery which has been developed in England and with adequate psychometric properties (described in Section 13.2). Since personal recovery is something experienced rather than assessed by an expert, a self-report measure was appropriate for clinical end-point. The timing between baseline and follow-up (*i.e*. the length of the intervention) was chosen as 12 months to allow sufficient time for team-level changes in practice to occur, be sustained, and have an impact.

The QPR has two sub-scales: intrapersonal (mean = 45.7, sd = 16.1, range 13-68) and interpersonal (mean = 14.0, sd = 3.7, 0-20). The sample size calculation is based on being able to detect a medium standardised effect size of 0.4 in both sub-scales, which equates to a difference of 6.4 points on the QPR intrapersonal subscale and 1.5 points on the interpersonal subscale.

The estimated sample size for a two-group comparison of means (alpha = 0.05, power = 0.8) is 99 per group. However, as this is a team-level intervention, the unit of randomisation is the team. An initial 29 teams (20 from SLaM, 9 from^2^gether) will be recruited, and we anticipate 17% attrition (due to team mergers or restructuring), giving a total of 24 teams (16 from SLaM, 8 from^2^gether). The same number of participants will be included from each team. Adjustment for clustering within teams assumes an intracluster correlation of 0.05, with equal numbers of clusters in each randomisation group. For 24 teams, 164 participants are needed per group, i.e. 14 participants per team. To allow for one participant (7%) drop-out per team, 15 participants per team will be recruited from the 29 teams. This drop-out rate is consistent with attrition in previous randomised controlled trials we have conducted [27].

The total initial sample is therefore 435 service users, comprising 225 in intervention and 210 in control. Based on the above attrition and clustering estimates, we anticipate this will produce an analysable sample of 336 participants, giving power to detect a medium effect size of 0.4 (alpha 0.05, power = 0.8) on both QPR sub-scales.

#### Secondary study

In a pre-planned sub-group analysis, we will also be investigating the outcomes of service users from black backgrounds in the SLAM site only. The primary outcomes for this sub-study will be the QPR (as above) and the Client Satisfaction Questionnaire - 8 item version (CSQ) [28], which produces a global satisfaction score (mean = 24, sd = 6) within this population. CSQ data were available from a previous study [29], from which a retrospective analysis of data from black individuals demonstrated an effect size of 0.67 for differences in CSQ between intervention and control groups. The sample size calculation for the secondary study is based on being able to detect a large effect size of 0.67, equating to a difference of 10.8 on the QPR intrapersonal subscale, 2.5 on the QPR interpersonal subscale, and 4 on the CSQ.

Using the same estimates for a two-group comparison of means as for the main study (20% SLaM team attrition, 7% participant attrition, 0.05 intra-cluster correlation, alpha 0.05, power 0.8), 6 participants per team will be recruited. The initial sample of 120 (20 teams × 6 participants) is anticipated to produce an analysable sample of 89 participants, giving power to detect an effect size of 0.67 on both QPR sub-scales and on CSQ.

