### Analysis plan

#### Objective 1: To establish the effectiveness of the intervention described in the REFOCUS manual

The two trial hypotheses will be investigated using standard intention-to-treat analysis for all participants with end-of-trial data. Firstly, to identify whether the intervention was associated with improved personal recovery (QPR) and secondly, whether it was associated with improved secondary outcomes at the end of the intervention. Individual level outcomes for staff and service users will be aggregated at the cluster level. Analysis of covariance (ANCOVA) will be used to adjust for baseline levels including clustering effects of teams and other baseline prognostic indicators. Sensitivity analysis will control for baseline covariates associated with missing data. Analysis will be blind to allocation status.

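### The sample sizes make no allowance for the small number of teams: on the stated inputs, secondary-study power is about 0.76 rather than 0.8, and main-study power is slightly below 0.8

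*Protocol article*

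**What the plan says.** In the protocol article, Sample size, Main study, the starting point is: "The estimated sample size for a two-group comparison of means (alpha = 0.05, power = 0.8) is 99 per group". The target is set there too: "The sample size calculation is based on being able to detect a medium standardised effect size of 0.4 in both sub-scales". Clustering then enters: "Adjustment for clustering within teams assumes an intracluster correlation of 0.05, with equal numbers of clusters in each randomisation group". The result is: "For 24 teams, 164 participants are needed per group, i.e. 14 participants per team". The number of teams expected to remain is also given: "giving a total of 24 teams (16 from SLaM" and 8 from the other Trust). With 14 people in each of 24 teams, the analysable sample is 336.

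Sample size, Secondary study carries the same estimates over to the SLaM teams alone. It recruits 6 people from each of 20 teams, allows for 20% team loss and 7% participant loss, expects 89 analysable people and states 0.8 power, "giving power to detect an effect size of 0.67 on both QPR sub-scales and on CSQ". The Abstract repeats the claims for both studies.

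Two other places fix the level of the analysis. The Design section says that "the unit of randomisation and analysis is the mental health team". The Analysis plan under Objective 1 says: "Individual level outcomes for staff and service users will be aggregated at the cluster level". That section also plans an analysis of covariance on baseline levels.

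**The concern.** A design effect corrects the variance of the treatment difference for clustering. It does not allow for the fact that, when team means are compared, that variance is estimated from only as many values as there are teams. With hundreds of people the normal and t distributions are interchangeable; with 24 team means the difference starts to show, and with 16 it is plain. The sizing is done as if the between-team variance were known, while the same document describes an analysis in which it must be estimated from 22 or 14 degrees of freedom at most.

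The secondary study has the fewest teams and is affected most. Recruitment and randomisation procedures also presents the sampling of 6 people per SLaM team as securing enough power for the secondary hypothesis, and that assurance rests on this calculation. The issue is separate from the number of scores tested, since it arises for a single score at 0.05.

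**Working it through.** **Inputs.** From Sample size, Main study: alpha 0.05, taken as two-sided because that reproduces 99; power 0.8; effect 0.4 SD; intracluster correlation 0.05; 24 teams, so 12 per arm with equal arms; 14 people per team. From Secondary study: effect 0.67 SD; 89 people; the same correlation, alpha and power. The 16 SLaM teams give 8 per arm and 89/16 = 5.5625 people per team.

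**Reproducing the plan's figures.**
- Individual size: 2 × ((1.960 + 0.842)/0.4)² = 98.1, rounded up to 99 per group.
- Design effect: 1 + (14 − 1) × 0.05 = 1.65. Then 99 × 1.65 = 163.35, rounded up to 164 per group.
- Main analysable sample: 24 × 14 = 336.
- Secondary analysable sample: 120 × 0.80 × 0.93 = 89.3, so 89.

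All four agree with the protocol.

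**Power with normal critical values.** In SD units, the variance of a team mean is 0.05 + 0.95/m. The standard error of the difference is √(2 × variance/teams per arm), and the noncentrality is effect/SE.
- Main: variance 0.05 + 0.95/14 = 0.1179; SE √(2 × 0.1179/12) = 0.1402; noncentrality 0.4/0.1402 = 2.854; power Φ(2.854 − 1.960) = 0.814.
- Secondary: variance 0.05 + 0.95/5.5625 = 0.2208; SE √(2 × 0.2208/8) = 0.2349; noncentrality 0.67/0.2349 = 2.852; power Φ(2.852 − 1.960) = 0.814.

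On this basis the stated 0.8 is met in both studies.

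**Power with a t distribution on teams minus 2 degrees of freedom.** The noncentralities are unchanged; the noncentral t replaces the normal.

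| | Main | Secondary |
|---|---|---|
| Degrees of freedom | 24 − 2 = 22 | 16 − 2 = 14 |
| Power at the stated effect | 0.779 | 0.756 |
| If site strata are also fitted | 0.767 (six sites, 17 df) | 0.738 (four Boroughs, 11 df) |
| Effect detectable at 0.8 power, no strata | 0.41 SD | 0.71 SD |

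The main figure already includes the slack from rounding up to 14 per team; at exactly 164 per group it is 0.773.

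**In points.** Secondary: 0.708 × 16.1 = 11.4 on the QPR intrapersonal sub-scale (stated 10.8) and 0.708 × 6 = 4.2 on the CSQ (stated 4). Main: 0.411 × 16.1 = 6.6 intrapersonal points (stated 6.4).

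**What baseline adjustment could recover.** Assume a team-level baseline to follow-up correlation r, which the document does not give. The variance is multiplied by 1 − r² and one degree of freedom is lost.

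| r | Main (21 df) | Secondary (13 df) |
|---|---|---|
| 0 | 0.777 | 0.751 |
| 0.2 | 0.793 | 0.768 |
| 0.3 | 0.814 | 0.789 |
| 0.4 | 0.843 | 0.820 |
| 0.5 | 0.881 | 0.860 |

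Power returns to 0.8 at r of about 0.24 (main) and 0.34 (secondary). With site strata fitted as well, the values are about 0.29 and 0.40.

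**The case against.** The strongest reply is that 0.78 and 0.76 describe an unadjusted comparison of follow-up team means, which is not what is planned. The sizing leaves out a penalty for few teams and also a gain from baseline adjustment, and correcting only the first is one-sided. The Measures section reports QPR test-retest correlations of 0.874 and 0.769. Those are individual-level values over an unstated interval, not 12-month team-level ones, and no such figure is given for the CSQ, but they make a team-level correlation of 0.3 to 0.4 plausible for the QPR. This stands, and it rules out saying that the trial as analysed will fall short of 0.8. It does not rescue the stated figure as derived, because the sizing credits no correlation.

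A second reply is that the shortfall is smaller than the uncertainty in the inputs. For the main study this is fair: an intracluster correlation of 0.04 instead of 0.05 gives 0.811 on the same 22 degrees of freedom. For the secondary study it is less so. The same change gives variance 0.04 + 0.96/5.5625 = 0.2126, noncentrality 0.67/√(2 × 0.2126/8) = 2.906 and power of only 0.771. The 0.67 SD target, taken from a retrospective analysis of an earlier study, is itself uncertain, but the power claim is made at that value.

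Third, 99, 164, 336 and 89 all reproduce by the method described, and the formula behind 99 is inferred rather than named. That is so: the sums are not wrong, and the fault is that the method does not match the stated level of analysis.

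A reader might also infer that the test will have an inflated type I error, because normal critical values were used for sizing. The document does not support this. It names no reference distribution for the analysis, and that choice may sit in the statistical analysis plan, which is not shown.

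**Conclusion.** The concern holds for the stated power and is material only for the secondary study. On the protocol's own inputs, for one score at two-sided 0.05 without baseline adjustment, secondary power is about 0.76 on 14 degrees of freedom, a shortfall of about 4.4 percentage points; 0.8 corresponds to about 0.71 SD. Main-study power is about 0.78 on 22 degrees of freedom, roughly 2 points short, or 0.8 at 0.41 SD, which is a minor correction.

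These results assume equal arms, equal team sizes, the team losses that the protocol anticipates, and a team-level comparison, as the Design and Analysis plan sections describe. It would be tempting to conclude that the trial is underpowered or needs more people. The documents do not support that: a moderate team-level baseline correlation would bring both studies back to 0.8. What cannot be said is that the sizing as written delivers 0.8, because it rests on no such correlation.

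**What to change.** Keep the enrolment. In Sample size, Secondary study, recompute power with a t distribution on team degrees of freedom and state either about 0.76 at 0.67 SD, or 0.8 at about 0.71 SD (about 11.4 QPR intrapersonal and 4.2 CSQ points). Alternatively, keep 0.8 and declare the team-level baseline correlation that it relies on: at least about 0.34, or about 0.40 if Boroughs are fitted. Make the matching small correction in Sample size, Main study (about 0.78 at 0.4 SD, or 0.8 at 0.41 SD, or a declared correlation of at least about 0.24, or about 0.29 with sites fitted), and align the Abstract.

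The cost is a few restated figures, slightly less favourable, with no extra participants and no change to the design. Objective 3 feeds this trial's parameters into the sizing of a future trial, so it also helps to have the method right here.
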